##### Healthcare utilisation

Single items will be used to assess use of three types of pharmaceuticals over the last 3 months: pain-reducing medication, mood-enhancing medication, medication for other health complaints. Response categories are ‘no’ (0 points), ‘regularly’ (e.g. daily) (1 point) and ‘as needed’ (1 point). Outpatient visits to physicians will be assessed as the number of visits in the last 12 months. The utilisation of outpatient therapies (e.g. physiotherapy) will be assessed as the number of therapies units used over the last 12 months. Hospitalisation within the last 12 months will be captured as a dichotomous variable (0: ‘no’ and 1: ‘yes’). The number of days of sick leave during the last 12 months will also be assessed.

##### Sickness absence benefits and disability pensions

Data on days in receipt of sickness absence benefits, days in regular employment, applications for and granting of a disability pension will be extracted from the GPI registers during the third year of the study. These variables are the secondary outcomes in our analyses of the effectiveness of medical rehabilitation.

#### Other measures

Data on other variables will be collected at baseline in order to provide a description of the study sample, to determine potential barriers to the use of rehabilitation services, to gain variables for estimating the propensity score, and to identify variables that might influence the effect of rehabilitation services.

##### Comorbidity

Comorbidity will be assessed using an adapted version of the German version of the Self-Administered Comorbidity Questionnaire [60, 61], using only the ‘impairments because of the corresponding health problem’ subscale.

##### Health behaviour

Physical exercise, cigarette smoking, body mass index and membership of a self-help group or organisation will be assessed as indicators of health-related behaviour.

##### Work stress and work environment

Physical job demands will be measured using five 4-point items that yield a total score ranging from 0 to 15 points [62]. Psychological job demands (six items), job insecurity (two items), support by supervisor and colleagues (two items), atmosphere at work (one item), and overall job satisfaction (one item) will be assessed using the short version of the Copenhagen Psychosocial Questionnaire [54, 55]. Total scores for these variables range from 0 to 100 points. Workplace bullying will be assessed with a single 5-point item [63]. We will also capture information about professional title, weekly working hours, fixed-term job contracts, size of enterprise and shift work.

##### Cognitions about and experiences with rehabilitation services

Motivational factors related to application for rehabilitation services will be assessed using a set of questions that was recently developed for the Third German Sociomedical Panel of Employees [64]. The questions include items about subjective need for rehabilitation (and reasons for not having such a need), intention to apply for a medical rehabilitation programme (and reasons for not intending to apply), knowledge of rehabilitation application procedures, negative outcome expectations, and support for the application for rehabilitation from family and friends and physicians and therapists.

##### Socio-demographic data

Age and sex will be derived from the GPI registers. Data on net income, job position, and educational level will be self-reported. Assessment of migrant status will be assessed based on Schenk’s recommendations [65]. Partnership status (single or partnered) and size of household, including number of children under 14 years and number of family members with a special need for care will also be assessed. Stress associated with housework and family commitments will be rated using two 11-point items (0: ‘not at all stressed’ to 10: ‘very stressed’) [66].

### Statistical analysis

#### Analysing barriers to rehabilitation utilisation

To identify barriers to the utilisation of medical rehabilitation services we will compare persons with back pain who complete a medical rehabilitation with persons with back pain who do not. We will identify barriers to use of rehabilitation services across the entire course of the rehabilitation process, from recognition of need for rehabilitation and applying for a medical rehabilitation programme, to applying successfully for a grant, participating in a rehabilitation programme and completing the programme. Different barriers apply to each step and these will be identified by analysing group differences in baseline values of the outcome and control variables at each stage of the process. The first step in the analysis will be univariate analyses: *t* tests and analyses of variances for continuous variables, Mann–Whitney *U* tests for ordinal variables and chi-squared tests for binary variables. The second step will consist of logistic regression analyses to identify the most important predictors of rehabilitation intention, rehabilitation application, acceptance onto a rehabilitation programme and use of rehabilitation. In the third step we will estimate generalised structural equation models to describe the direct and indirect effects of potential barriers.

#### Propensity score matching

Rehabilitation participants and untreated subjects will be matched by propensity scores to achieve a balanced sample and enable calculation of unbiased estimates of effectiveness [67–72]. The propensity score is the conditional probability of receiving the treatment under evaluation (i.e. the medical rehabilitation programme) given the vector of observed background variables. Matching by propensity scores allows one to obtain a sample in which the treated and untreated groups are balanced, if there is sufficient overlap between their propensity scores. Propensity score matching also allows one to avoid the dimensionality problem that affects conventional direct matching procedures involving multiple variables, e.g. age, sex, socioeconomic state, depression, work ability, by reducing the matching requirement to a single dimension.

The propensity score will be estimated using a logistic regression model including all variables that are associated with treatment allocation. For every treatment case three persons with a similar propensity score will be selected from the larger pool of non-treatment cases. Re-sampling with replacement will be used to reduce bias. If it is necessary to achieve a balanced sample, a caliper of one-quarter of the propensity score will be used during re-sampling. Additional matching schemes will be used in the sensitivity analysis.

Standardised percentage bias will be calculated as an indicator of bias before and after matching due to differences in observed sample characteristics. This is the difference between sample means in the intervention and control groups relative to the square root of the average of the sample variances in both groups [73]. Multiple imputations will be used to fill in missing data before propensity scores are estimated. The propensity scores for each record will be averaged across the completed datasets and propensity score matching will be performed with these averaged scores [74].

#### Estimating the treatment effect

The average treatment effect for the treated cases will be estimated with weighted linear regression models in the case of continuous outcomes and generalised linear models in the case of binary outcomes (see above: primary outcome and secondary outcomes) [75]. Robust standard errors will be calculated.

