**Methods:**

In 2017 a postal questionnaire will be sent to 45,000 persons aged 45 to 59 years whose pension insurance contributions are managed by the GPI North or the GPI Central Germany. In 2019 respondents who report back pain in the first survey (*n* = 5760 expected) will be sent a second questionnaire. Individuals will be eligible for the first survey if they are employed, have neither used nor applied for a rehabilitation programme during the last 4 years and neither received nor applied for a disability pension. The sample will be drawn randomly from the registers of the GPI North (*n* = 22,500) and the GPI Central Germany (*n* = 22,500) and stratified by sex and duration of sickness absence benefits. Barriers to rehabilitation services will be related to socio-demographic and social characteristics, pain and attitudes to pain, health and health behaviour, healthcare utilisation, experiences and cognitions about rehabilitation services and job conditions. Propensity score matched analyses will be used to examine the effectiveness of rehabilitation services. Data on use of medical rehabilitation will be extracted from administrative records. The primary outcome is pain disability. Secondary outcomes are pain intensity and days of disability, pain self-efficacy, fear avoidance beliefs, self-rated health, depression, healthcare utilisation, self-rated work ability and subjective prognosis of employability, sickness absence benefits, and disability pensions.

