### Sample size estimation

Estimates for baseline response (40%), consent to linking survey with administrative data (80%), back pain (40%) [48], utilisation of rehabilitation (8%) and response to follow-up (60%) are derived from other studies. In case of a 1-to-3-matching of rehabilitants and controls, the final sample of 276 rehabilitants and 828 untreated controls is sufficient to detect a minor difference in the primary outcome between rehabilitants and controls (standardised mean difference = 0.2; two-tailed alpha = 0.05) with a power of 0.82. (Fig. 1).

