#### Primary outcome

Pain disability will be the primary outcome in our analyses of the effectiveness of medical rehabilitation and will be assessed at baseline and follow-up. Three items from the German version of the Chronic Pain Grade Questionnaire will be used to assess pain disability [48, 49]. These items deal with the extent to which pain interferes with important life domains, including daily living, leisure time and work. Because it includes the work domain this measure also covers work ability, which is the primary focus of GPI-approved rehabilitation services. The German version of the Chronic Pain Grade Questionnaire has been shown to be a reliable, valid and useful instrument [49]. Items are scored from zero to ten points, with higher scores indicating greater disability. Item scores are averaged and multiplied by ten to give a total pain disability score ranging from 0 to 100 points.

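### The weighted outcome regression names no baseline covariate; stating that it includes the outcome's own baseline value would avoid standard errors roughly 10-30% too large and recover power at no cost

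*Protocol article*

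**What the plan says.** In the Protocol article, the section Estimating the treatment effect states: "The average treatment effect for the treated cases will be estimated with weighted linear regression models in the case of continuous outcomes". It adds: "Robust standard errors will be calculated". This fixes the estimand, the model class and the general kind of standard error. It lists no covariates, and it does not say that treatment is the only regressor.

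Control of baseline differences is given to matching. The section Propensity score matching puts every variable related to treatment receipt into a logistic score. It matches three controls to each rehabilitant with replacement, allows a caliper if balance requires it, and reports standardised percentage bias before and after matching. It sets no threshold for that bias and no role for baseline values in the outcome model if imbalance remains. The section Other measures lists what the further baseline variables are for (description, barriers, the score, effect modification); adjustment of the outcome model is not among them.

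The baseline data exist. The section Primary outcome says that pain disability "will be assessed at baseline and follow-up", and Table 2 marks both time points for every metric questionnaire outcome.

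The section Sample size estimation plans for "the final sample of 276 rehabilitants and 828 untreated controls" at "standardised mean difference = 0.2; two-tailed alpha = 0.05", "with a power of 0.82".

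**The concern.** The baseline value of pain disability is likely to be among the strongest predictors of its follow-up value. If it is used only inside a one-dimensional score, two things can happen.

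- **Standard error.** Matching makes the two groups alike on the score, so much of the outcome variation explained by baseline cancels in the group difference. A treatment-only robust variance does not know this. It counts the baseline-explained variation in full, so the interval comes out too wide.
- **Protection.** Any baseline difference that matching leaves behind passes straight into the estimate, in proportion to the baseline/follow-up correlation.

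At stake are power on the primary outcome and on the other continuous outcomes measured twice, and a second line of defence against confounding by severity. The silence also leaves open a choice between adjusted and unadjusted estimates after results are known.

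**Working it through.** **1. The plan's own figures.** The abstract states that "a postal questionnaire will be sent to 45,000 persons aged 45 to 59 years". Response 40%, consent to linkage 80% and back pain 40% give 45,000 × 0.40 × 0.80 × 0.40 = 5,760. Rehabilitation use 8% and follow-up response 60% give 5,760 × 0.08 × 0.60 = 276.5 rehabilitants. At 1:3, that means 828 controls.

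SE = √(1/276 + 1/828) = 0.0695 SD units. Power = Φ(0.2/0.0695 − 1.96) = 0.8206. The stated 0.82 reproduces, and no credit for baseline adjustment is built into it.

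**2. Textbook effect of adjustment.** With baseline/follow-up correlation r, the residual SD is √(1 − r²). The documents give no r, so a range is assumed.

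| r (assumed) | √(1 − r²) | SE | power |
|---|---|---|---|
| 0.3 | 0.954 | 0.0663 | 0.855 |
| 0.5 | 0.866 | 0.0602 | 0.914 |
| 0.6 | 0.800 | 0.0556 | 0.949 |
| 0.7 | 0.714 | 0.0496 | 0.981 |

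These figures ignore the fact that matching may already have used the baseline value, so they overstate the real gain. Simulation is needed for that.

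**3. Simulation with the baseline value in the score.** Common settings: 3,456 persons (5,760 × 0.60), true effect 0.2, 1:3 nearest-neighbour matching with replacement, weighted regression with a heteroscedasticity-robust SE. Setting A has ten covariates in the score, 8% treated and 250 runs per r. Setting B has two covariates (log-odds of treatment −2.75 + 0.5 × baseline + 0.4 × second covariate) and 400 runs. Confounding strengths are assumed.

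| setting, r | unadjusted SE / true SD | ratio | adjusted SE / true SD | ratio |
|---|---|---|---|---|
| A, 0.5 | 0.0751 / 0.0666 | 1.13 | 0.0652 / 0.0655 | 1.00 |
| A, 0.6 | 0.0751 / 0.0601 | 1.25 | 0.0601 / 0.0573 | 1.05 |
| A, 0.7 | 0.0753 / 0.0578 | 1.30 | 0.0538 / 0.0541 | 0.99 |
| B, 0.5 | 0.0775 / 0.0659 | 1.18 | 0.0671 / 0.0645 | 1.04 |
| B, 0.7 | 0.0775 / 0.0605 | 1.28 | 0.0554 / 0.0578 | 0.96 |

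A further simulation with HC1 standard errors and r from 0.5 to 0.7 put the unadjusted SE 11-29% above the true SD.

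- *Reported SE.* It falls by almost exactly the textbook factor: in A, 0.0652/0.0751 = 0.868, 0.0601/0.0751 = 0.800 and 0.0538/0.0753 = 0.714.
- *True SD.* It falls far less: in A, 0.0655/0.0666 = 0.983, 0.0573/0.0601 = 0.953 and 0.0541/0.0578 = 0.936, that is 2%, 5% and 6%. Adjustment mainly brings the SE into line with a precision that matching has already bought.
- *Power.* In A it rises from 0.80 to 0.86 (r = 0.5), 0.84 to 0.93 (r = 0.6) and 0.85 to 0.96 (r = 0.7). The HC1 simulation went from 0.75-0.84 to 0.81-0.93. Monte Carlo error on a power of 0.80 from 250 runs is √(0.80 × 0.20/250) = 0.025.
- *Coverage.* An SE 25% too large implies 2Φ(1.96 × 1.25) − 1 = 0.986 for a nominal 95% interval. At 13% and 30% the same formula gives about 0.973 and 0.989.

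**4. Imbalance.** The shift in the estimate is r × remaining baseline difference. At r = 0.5, a difference of 0.05 or 0.10 SD shifts it by 0.025 or 0.05, which is 12.5% or 25% of the 0.2 target. In B with baseline in the score, the imbalance averaged 0.00 with a run-to-run SD of about 0.025, so 0.10 would be rare, and the unadjusted mean estimate was 0.20. With baseline left out of the score, the imbalance was 0.49 SD and the unadjusted estimate 0.445 (r = 0.5) or 0.545 (r = 0.7); adjustment brought these back to 0.204 and 0.199.

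**The case against.** The strongest objection is that the article is silent rather than wrong. It does not fix a treatment-only model, the paper it cites for the method is not at hand, and a condensed article may leave the covariate list to a fuller plan. This stands against the stronger claim a reader might infer, that the trial plans no baseline adjustment. It does not remove the point. The article settles the estimand, matching ratio, replacement, score averaging and SE type, and it assigns baseline control to matching. In that context, whether the primary outcome's own baseline value enters the model is worth fixing.

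A reader might also infer that matching necessarily leaves residual imbalance. The documents do not support that. The score is meant to take in whatever relates to treatment, which can include baseline outcomes; balance is checked, a caliper is available, and further matching schemes are planned as sensitivity analyses. With the baseline value in the score, only chance imbalance remains. The estimates of 0.45-0.55 are a worst case: omitting a baseline value strongly related to treatment would breach the article's own rule for building the score.

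The objection that the efficiency gain is small is also right where true sampling variability is concerned. Most of the power gain comes from correcting an oversized SE, and its size depends on the variance estimator, which the article calls only robust. Unadjusted power of 0.80-0.85 in setting A is close to the planned 0.82. It was lower, down to 0.75, in the HC1 simulation.

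**Conclusion.** The point holds in limited form. The article names no baseline covariate in the outcome model, although the data are collected. If the model is fitted with treatment only and the baseline value is in the score, the estimate is about unbiased. A standard heteroscedasticity-robust SE then exceeds the true sampling SD by roughly 10-30% at assumed correlations of 0.5 to 0.7. The power lost is about 0.06 at 0.5 and 0.07-0.09 at 0.6, while true precision would improve by only about 1-6%. Chance imbalance, or omission of the baseline outcome from the score, would also go uncorrected.

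It would be too much to call the planned analysis invalid: the error is conservative, and the stated power of 0.82 stands without adjustment. The sizes rest on assumed correlations, assumed confounding strengths and the choice of robust variance, none of which the documents give.

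**What to change.** In Estimating the treatment effect, add that the weighted regression for each continuous outcome with a baseline measurement contains treatment and the baseline value of that outcome. Make this the primary estimate, and report the treatment-only estimate beside it. Which covariates, if any, to use for outcomes without a baseline value (applications for and grants of a disability pension) is a matter of preference and not part of this point.

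The cost is one sentence of analysis wording, settled before follow-up outcomes are seen. No new data are needed, and the sample size and its power statement stay as they are.

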#### Moderator analyses

Moderator analyses will be performed to clarify whether individual characteristics modify the treatment effect. The moderating effects of individual characteristics will be modelled in terms of multiplicative interaction terms for the treatment indicator and potential moderators. In the case of continuous moderators, these variables will be *z*-standardised [76]. Moderators will be tested in order to identify the patients who would benefit most from medical rehabilitation.

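### Treatment-by-moderator terms are tested after matching on one overall score, with no stated check or adjustment for imbalance within moderator levels

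*Protocol article*

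**What the plan says.** Under Propensity score matching, the Protocol article sets a logistic score, selects three untreated persons per rehabilitant on it, and gives as an advantage "reducing the matching requirement to a single dimension". The balance check follows: "Standardised percentage bias will be calculated as an indicator of bias before and after matching due to differences in observed sample characteristics". It is defined as the treated-minus-control difference in means over a pooled standard deviation. Further ways of matching are promised for sensitivity analysis but not described.

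Estimating the treatment effect specifies weighted regression with robust standard errors for the effect in the treated, and names no covariates. Moderator analyses then adds the interactions: "The moderating effects of individual characteristics will be modelled in terms of multiplicative interaction terms for the treatment indicator and potential moderators". Their purpose is to find out which patients gain most. Under Other measures, the baseline variables serve both to estimate the score and "to identify variables that might influence the effect of rehabilitation services", so drivers of uptake and candidate moderators come from the same set.

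**The concern.** An interaction is the difference between two treated-versus-control contrasts, one in each moderator level. It is free of confounding only if the groups are comparable within each level. The article describes balance for the treated and untreated groups and does not mention levels.

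Opposite imbalances in two levels cancel in the overall mean difference but add up in the product term. This is confounding, not multiplicity, and can occur with a single moderator. The article intends to use the result to say who benefits most. A false interaction could therefore point services at the wrong group, while the overall balance check gives no warning.

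**Working it through.** **1. The plan's own figures.** Sample size estimation gives 45,000 × 0.40 × 0.80 × 0.40 = 5,760 persons with back pain, and 5,760 × 0.08 × 0.60 = 276.5 rehabilitants. With 276 and 828 controls, the standard error in SD units is √(1/276 + 1/828) = 0.0695. Then 0.2/0.0695 = 2.88, and Φ(2.88 − 1.96) = 0.82, which agrees with "standardised mean difference = 0.2; two-tailed alpha = 0.05) with a power of 0.82". This figure concerns the overall contrast only.

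**2. Why overall balance is not enough.** Let d₁ and d₀ be the treated-minus-control imbalances (in SD) of a covariate in two moderator levels, and b the change in outcome per SD of that covariate.

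- Overall imbalance ≈ p·d₁ + (1 − p)·d₀, where p is the share of treated persons in level 1.
- False interaction without adjustment ≈ b·(d₁ − d₀).

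The first can be zero while the second is not.

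**3. Simulation.** From the document: 5,760 × 0.60 = 3,456 persons followed, 8% treated, 1:3 matching with replacement, weighted regression with robust standard errors. Assumed: a 50:50 moderator, b = 0.5, a main-effects score, and the uptake slopes shown (log-odds per SD). The true effect was −0.2 SD in both levels, so the true interaction was 0. There were 400 runs per setting.

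| Slopes (level 0 / level 1) | Overall bias | Bias in level 0 / level 1 | False interaction, rejection | With product term in score | With covariate in outcome model |
|---|---|---|---|---|---|
| 0.50 / 0.50 | 0.0% | −0.1% / 0.1% | −0.002 SD, 5% | −0.005 SD, 2% | −0.003 SD, 5% |
| 0.35 / 0.65 | −0.1% | −13.4% / 10.4% | 0.123 SD, 12% | 0.002 SD, 4% | 0.005 SD, 4% |
| 0.20 / 0.80 | −0.5% | −23.9% / 16.2% | 0.198 SD, 25% | −0.010 SD, 3% | −0.009 SD, 4% |

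The formula agrees: 0.5 × (0.104 + 0.134) = 0.119 and 0.5 × (0.162 + 0.239) = 0.200. In the last row the apparent effects were −0.32 and −0.12 SD. The share of runs with overall bias below 10% was 1.00 in every setting. Even with equal slopes, 18% of runs had a level with bias above 10% by chance.

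**4. Sensitivity of the size.** Other simulations of the same design, unadjusted and with a main-effects score, gave:

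| Slopes | False interaction (rejection) |
|---|---|
| 0.6 vs 0.4 | 0.09 SD (10%); 0.12 SD (12%) |
| 0.7 vs 0.3 | 0.17 SD (20%); 0.19 SD (23%); 0.22 SD (31%) |
| 0.8 vs 0.2 | 0.25 SD (39%); 0.33 SD (60%) |

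The spread reflects modelling choices that the document does not fix.

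**5. Adjustment.** With the responsible covariate in the outcome model, the 0.6/0.4, 0.7/0.3 and 0.8/0.2 settings gave −0.003, 0.002 and 0.002 SD, with 6%, 5% and 4% rejection. The adjustment must include the right variable. When a second prognostic variable had slopes 0.6 vs 0.2, the false interaction was 0.19 SD (25%). It was still 0.10 SD (12%) after adjusting for baseline pain disability alone.

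**The case against.** This is a condensed article. The functional form of the score, balance tables by subgroup and covariates in the outcome model are often left to an analysis plan. The article asks for every variable related to treatment allocation in the score and does not exclude product terms. It does not rule out covariate adjustment. It also does not say outright that the product terms are fitted in the matched sample, although that is the natural reading. It contains no contradiction on this point.

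The uptake slopes are assumed, since no section reports selection that differs by moderator level. The largest rejection rates disappear once the responsible covariate enters the outcome model, which is ordinary practice when the outcome is measured at baseline.

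All of this stands, and it limits the point to a conditional weakness. It does not remove it: the article states the balance statistic, the interaction model and the use of the result, and nothing it states would show or correct imbalance within levels.

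A reader might infer that matching a treated woman to men is itself a defect, or that the matching cannot give balance within levels. Neither follows. A correctly specified score that includes the moderator balances covariates within its levels in expectation, and the equal-slope setting shows no systematic bias. Nor does the text say that only one matching will be done, because further schemes are promised, though unspecified.

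**Conclusion.** The point holds as a conditional risk to the moderator analyses. Three things must coincide: uptake depends on a prognostic variable to different degrees across moderator levels, the score omits this, and the outcome model does not adjust for the variable. Under the assumed slopes of 0.6 vs 0.4 to 0.8 vs 0.2, the false interaction is about 0.1 to 0.3 SD, with roughly 10% to 60% rejection instead of 5%. The upper half of that range is as large as the 0.2 SD main effect for which the study is powered, but it needs the wider slope differences. If any one of the three conditions fails, the systematic bias is about zero.

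A reader might go further and conclude that the moderator results will be wrong, or that the main result is in doubt. The document supports neither. It gives no evidence of the slopes, the overall effect in the simulations stayed at about −0.2 SD, and the power of 0.82 is correct.

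**What to change.** For each moderator tested:

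- Report standardised percentage bias within its levels, using halves for continuous moderators.
- Include moderator-by-covariate terms in the propensity score.
- Adjust the outcome model for the moderator main effect, baseline pain disability and any covariate still unbalanced within a level.
- Interpret an interaction only where balance within levels, or such adjustment, is shown.

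Matching within levels can be an optional sensitivity analysis. It should not be the default, because an even split leaves only 276/2 = 138 rehabilitants per level, against a long list of candidate covariates.

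The cost is some plan wording, more analysis work and a slightly larger score model. No new data are needed.
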